### Study approach

2.3

This FIH study will consist of two parts: a dose-escalation part comprising an accelerated titration phase in which the dose level (DL) is fixed for the individual patient but may increase with each patient by up to 100%, depending on safety considerations judged by an SRC. In case of CC-3–induced adverse events (AEs) ≥grade 2 according to Common Terminology Criteria for Adverse Events (CTCAE) version 5.0, dose-limiting toxicity, reaching a DL of ≥800 µg or SRC decision, this accelerated titration phase will be switched to a standard 3 + 3 dose–escalation design. At this stage, dosing will be split in a priming dose (last DL of the accelerated titration part with no AE ≥2 and no DLT) and a target dose (DL at which the stopping criterion was observed that terminated the accelerated titration part). Three patients will be enrolled in this first cohort. If one of these three develops DLT, then three additional patients will be recruited into the cohort. If two patients develop DLT, then the dose is de-escalated to the last DL considered as safe. If no patient of this cohort experiences DLT, then the next DL will be determined by the SRC and applied to a second cohort. This will again consist of three patients and follow the same DLT considerations as the previous cohort. This will be repeated until MTD is determined, with MTD defined as no more than one of the six patients experiencing DLT. Once the MTD is determined, dosing will be fixed at this level. Then, further patients will be recruited until 20 patients altogether have received CC-3 at the MTD. This dose-expansion part will serve to confirm the RP2D and to detect first signs of clinical efficacy (see also **Figures 1**, **2**).

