In case AE-fulfilling criteria for DLT occur, additional patients are enrolled into the cohort. If two patients experience DLT, then the dose is de-escalated to the previous lower DL that was formerly considered to be safe, and, further, patients receive this lower DL until a total of six patients have been treated or further DLTs develop. If two of the four or two of the six patients experience a DLT, then the DL will be de-escalated to the next lower DL formerly considered to be safe, and patients will receive this lower DL until a total of six patients have been treated (**Figure 2B**). MTD is defined as the DL at which none or one patient experienced a DLT. Once the MTD has been defined, the dose-escalation part of the study is terminated and the dose-expansion part commences.

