### Safety/dose-limiting toxicity

2.9

Toxicity will be graded according to the National Cancer Institute CTCAE (v5.0) and the CRS grading system by Lee et al. (36). All AEs and SAEs will be documented and reported according to good clinical practice guidelines. Furthermore, we will report on AESIs, which include occurrence of CRS, infusion-related reactions upon study drug administration and drug induced liver injury (DILI). These AESIs will be monitored closely and included in patient safety narrative reports to the data safety monitoring board (DSMB).

DLT is defined as any AE grade ≥3 that the investigator considers to be at least possibly related to study treatment and occurring within the DLT safety period (from first study drug treatment to day 21 or 28, respectively, if an additional intermittent priming dose is given) with few exceptions. Notably, grade ≥3 CRS lasting less than 48 h, grade ≥3 nausea, vomiting or diarrhea in patients who have not received optimal antiemetic or antidiarrheic treatment, as well as isolated ≥3 laboratory abnormalities resolving within 7 days and without clinical sequelae are not considered a DLT. Likewise, liver toxicity caused by obstruction, metastasis, or infection; grade ≥3 transaminitis or direct hyperbilirubinemia for <4 days; grade 3 fatigue for ≤5 days; grade 3 infusion reaction resolving within 8 h; nor grade 3 but adjustable (i.e., not refractory) arterial hypertension are not considered a DLT.

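### Two DLT exemptions in section 2.9 set different time limits for the same isolated liver-value rise (7 days against under 4 days), and the article does not say which one governs

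*Protocol article*

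**What the plan says.** The protocol article, section 2.9 (Safety/dose-limiting toxicity), starts from a general rule: "DLT is defined as any AE grade ≥3 that the investigator considers to be at least possibly related to study treatment", within a window of 21 days, or 28 days if an intermittent priming dose is added. Exceptions follow in two consecutive sentences.

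- The first sentence includes a laboratory exemption: "isolated ≥3 laboratory abnormalities resolving within 7 days and without clinical sequelae are not considered a DLT".
- The second sentence continues the same list and includes a liver exemption: "grade ≥3 transaminitis or direct hyperbilirubinemia for <4 days".

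Neither sentence refers to the other. The laboratory exemption does not exclude liver values, and the liver exemption does not say that it replaces the laboratory one.

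The resulting DLT count drives the dose decisions. Section 2.3 adds three patients after one DLT in three and then says: "If two patients develop DLT, then the dose is de-escalated to the last DL considered as safe". Section 2.7.1 says: "MTD is defined as the DL at which none or one patient experienced a DLT". Section 2.10 makes a DLT a trigger for a report to the DSMB.

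**The concern.** A transaminase or direct bilirubin rise is a laboratory abnormality. If it is isolated, drug-related, of grade ≥3 and without sequelae, both exemptions describe it, with different time limits. Two careful readers can then classify the same event differently. One treats the list as cumulative, so that meeting any one exception is enough. The other lets the specific rule on liver values displace the general rule on laboratory values. Both are ordinary ways to read such a list.

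The classification feeds cohort expansion, de-escalation and the MTD, and the MTD fixes the dose for the expansion part, where 20 patients in total are to receive it. Liver events are also foreseeable here. Drug-induced liver injury is one of the named adverse events of special interest, and section 2.5 admits patients with hepatic metastases whose ALT and AST are up to 5 × ULN and whose bilirubin is up to 2.5 × ULN.

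**Working it through.** The article states no figure that depends on this wording, so there is none to reproduce. The check sets the two exemptions side by side and then follows one event through the 3 + 3 rules.

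**Inputs (section 2.9)**

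- Laboratory exemption: isolated, no clinical sequelae, resolves within 7 days.
- Liver exemption: transaminitis or direct hyperbilirubinemia for under 4 days, with no condition on isolation or sequelae.
- Test event: an isolated grade ≥3 transaminase rise, at least possibly drug-related, without sequelae, and not caused by obstruction, metastasis or infection (those causes have their own exemption).

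**Step 1: classify by duration in whole days**

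| Duration | Laboratory exemption met | Liver exemption met | If any one exemption suffices | If the liver limit governs |
|---|---|---|---|---|
| 1–3 days | yes | yes | not a DLT | not a DLT |
| 4–7 days | yes | no | not a DLT | DLT |
| 8 days or more | no | no | DLT | DLT |

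The readings differ only at 4 to 7 days. This measures both limits on the same clock. If one counts time at grade ≥3 and the other counts time to full resolution, the edges of the window move, hence about 4 to 7 days.

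**Step 2: effect on the design**

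- In the standard titration phase, one reclassified event can turn 0/3 into 1/3. The cohort then takes three more patients instead of moving on.
- It can turn 1/6 into 2/6. The dose is then de-escalated instead of meeting the MTD definition.
- In the accelerated phase the switch to 3 + 3 does not hinge on the classification. Section 2.7.1 already triggers it for any AE of grade ≥2 not unequivocally due to another cause. Only the DSMB report would differ.

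**Step 3: illustration with assumed rates, none of them in the article**

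Let p be the DLT rate per patient. The chance that a dose passes a plain 3 + 3 cohort is (1−p)³ + 3p(1−p)² × (1−p)³.

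- p = 0.10: 0.729 + 0.243 × 0.729 = 0.906.
- p = 0.15: 0.614 + 0.325 × 0.614 = 0.814.
- p = 0.20: 0.512 + 0.384 × 0.512 = 0.709.

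If other DLTs occur at 10% and liver events in the 4-to-7-day window add 0, 5 or 10 percentage points when counted, the pass probability is 0.906, 0.814 or 0.709. This shows the direction and the mechanism. It does not estimate the effect in this trial, and it ignores the SRC's option to enlarge a cohort to nine.

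**The case against.** **The list is cumulative.** On a plain reading, an event that meets one exception is exempt, and no sentence says that transaminitis of 4 days or more is a DLT despite meeting another. This stands in part. A reader might infer that the same event is at once a DLT and not a DLT, but the documents do not support that: there is a coherent reading under which the day-5 rise is simply exempt. What remains is that the text does not settle on this reading, and the specific-over-general reading is also reasonable.

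**The liver limit still has work to do.** A reader might also infer that the 7-day rule leaves the liver limit without effect. That is not so. The laboratory exemption requires an isolated abnormality without sequelae, and the liver exemption requires neither. The liver exemption therefore still covers short liver events that are not isolated or have sequelae.

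**CRS and infusion reaction.** A reader might see the same conflict between "grade ≥3 CRS lasting less than 48 h" and "grade 3 infusion reaction resolving within 8 h". It is not one. Section 2.9 names these as separate events, and different limits for different events are no contradiction. Which label an acute reaction receives is a question of attribution. These events therefore do not belong in the size of the problem.

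**An article condenses the protocol.** The list is introduced as a selection, and the full protocol, which is not shown, may state the precedence. This lowers certainty about the trial's actual rule. It does not remove the point, because the article itself prints two limits that cover one event.

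**Central review.** One SRC reviews all safety data and sets the next dose, so unnoticed divergence between sites is less likely. The SRC would still have to choose a reading, and the article gives it none.

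**Conclusion.** The point holds for liver laboratory values only, as an unstated precedence between two exemptions. An isolated, drug-related grade ≥3 transaminase or direct bilirubin rise without sequelae that lasts about 4 to 7 days can be counted either way. A single such event is enough to change a cohort decision, and so possibly the MTD and the dose taken into expansion. How often this would happen cannot be derived from the article, and the pass probabilities in the illustration rest wholly on assumed rates. The conclusion assumes that transaminase and direct bilirubin rises count as laboratory abnormalities, that both limits run on the same clock, and that the full protocol does not already settle the matter. No view is taken on which limit is right.

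**What to change.** Reconcile the two exemptions in section 2.9 so that an isolated transaminase or direct bilirubin rise falls under one rule. State whether these values are carved out of the 7-day laboratory exemption or governed by it, and that the SRC applies this single rule whenever DLTs are counted. The sponsor decides which limit applies. If the full protocol already states the precedence, carrying that statement into the article is enough.

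The cost is a sentence or two in section 2.9 and the matching DLT page of the case report form. No additional data are needed. It should be settled before DLTs are counted in the standard titration phase, so that the choice is not made with a particular event in view.

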### SRC and DSMB

2.10

Trial conduct will be overseen by an SRC composed of at least three members, including the coordinating investigator and a representative of the sponsor. It receives reports routinely 21 days after first dose of CC-3 of each single patient in the accelerated titration phase and as soon as three patients per cohort have completed the DLT evaluation period of 21 days after target dose application in the standard titration phase. The SRC assesses all available data on safety, PK, and PDK and determines the dose for the next cohort.

The DSMB is composed of three independent experts assessing study progress and safety data. It receives reports routinely after the end of the accelerated titration phase, after the end of the standard titration phase, upon request by the SRC, or in case of occurrence of DLT.

### Sample size calculation

2.11

The total sample size of the trial is assumed to be approximately 77 patients but depends on the observed safety profile, the number of dose cohorts evaluated, and the number of patients per cohort in the dose-escalation part and can therefore vary. Assuming a dose increase of 50% between cohorts, one treated patient per cohort in the accelerated phase (in total three cohorts), six treated patients per cohort (in total 10 cohorts) in the standard titration phase, a starting dose of 50 µg and a tested dose of 4,000 µg, and the estimated number of patients in the dose-escalation part is 63. In the dose-expansion part, up to 20 patients will be treated with the MTD. In this way, we will be able to estimate within a single-stage phase II design an objective response. For this purpose, objective response will be defined as SD, PR, or CR estimating P0 as the maximum response proportion of a poor drug of ≤20% of the patients and P1 as the minimum response proportion of a good drug of ≥50% with a power of 80% and a type one error of 5%. To this aim, we will need n = 17 evaluable patients assuming a dropout rate of 15% (n = 3).

### Patient and public involvement

2.12

CC-3 production (in accordance to good manufacturing practice) and trial conduct are exclusively funded by public resources without contribution from pharmaceutical industry or commercial organizations. Prior to approval of funding, proposals were peer reviewed in a competitive manner by the Helmholtz Validation Fund and the Joint Funding Program of the German Cancer Consortium. Extensive interaction consistently maintained with multiple patient representative groups in the framework of the alliance for patient participation in cancer research of the National Center for Tumor diseases (NCT) will substantially support our comprehensive efforts to inform patients about the beginning of study as well as patient recruitment.

### Data handling and storage

2.13

All findings including clinical, radiological, and laboratory data will be documented by the investigator or an authorized member of the study team in the electronic case report form. The investigators guarantee the privacy of patients. All personal data are treated according to the European general data protection regulation (EU 2016/679) and the German law. The data will be stored for 25 years. All data entry, modification or deletion, will be recorded automatically in an electronic trail. Monitoring of data will be conducted on a regular basis as well as prior to each safety report for SRC and DSMB.

## Discussion

3

As of now, metastatic CRC is an often rapidly progressive disease without curative treatment options. Here, we introduce a planned FIH study evaluating the safety and efficacy of the bispecific CD276xCD3 antibody CC-3 in patients with CRC after failure of third-line therapy. CC-3 was developed in our laboratory in a novel IgG-like format (IgGsc) to overcome several problems of so far available bsAbs. CC-3 not only comes with a prolonged serum half-life but also acts in a fully target-restricted manner with accordingly reduced off-target T-cell activation, resulting in reduced side effects (37, 38).

CD276, the target antigen of CC-3, is expressed on both tumor cells and tumor vessels of CRC. Thereby, a “dual mode of anticancer action” is enabled: On the one hand, targeting the tumor vessels should allow for improved influx of T cells into the tumor site via the damaged endothelial barrier. This should then be followed by an effective destruction of the tumor cells. Thereby, we expect to overcome a critical factor that so far limits the success of T cell-based immunotherapy of solid tumors (21, 39, 40).

Considering the lack of effective treatment options and the dismal prognosis of the study patient population, the expected benefits of CC-3 treatment in this clinical study outweigh the potential risks, especially because multiple risk mitigation measures have been implemented. The progress and safety data will be closely monitored by an SRC. Moreover, it will be regularly analyzed by the three independent experts of the DSMB. The SRC will carefully supervise the determination of the MTD, ensuring safe treatment of the study patients during dose escalation. The DSMB will counsel the coordinating investigator and the sponsor on whether to alter the trial protocol or discontinue the trial altogether.

In addition, the implemented one-patient-cohort escalation of CC-3 in the accelerated titration part is considered to benefit the patients included in this trial. Usually, the focus of phase I clinical trials is primarily set on safety and tolerability, and patients enrolled during early phases of a trial frequently do not receive sufficiently effective doses. This problem is addressed in our trial by our approach to rapidly increase CC-3 DLs in order to reach preclinically effective doses already in patients included early in the study. If no DLT is observed, then DL may be increased by up to 100% from one patient to the next, enabling an exponential dosage increment allowing to reach the maximum dose of 4,000 µg already with the 14th patient in case no DLT occur. A dose expansion part will then follow the dose-escalation part to collect first signs of efficacy and define the RP2D.

With the CC-3 antibody showing convincing preclinical activity, we expect that the study will demonstrate a corresponding clinical efficacy regarding objective tumor response and disease control rate, leading to a due benefit for this particular patient population through a trial that is fully funded by public resources.

## Ethics and dissemination

4

The study will be performed in accordance with the Declaration of Helsinki and will comply with the International Conference on Harmonization and Good Clinical Practice. In particular, no study examinations or treatments will be undertaken without first obtaining written informed consent from the patients. This trial is funded by research grants from the Helmholtz Validation Fund (Colomab) and the Joint Funding Program of the DKTK. The CC-3 study was approved by the Ethics Committee of the Medical Faculty of the Heinrich Heine University Düsseldorf and the Paul-Ehrlich-Institut, Germany (P00702). During trial conduct, the responsible authorities will be informed on a regular basis about the progress of the trial. The results of this clinical trial will be presented at relevant national and international meetings and published in peer-reviewed journals regardless of outcome. All planned publications will be reviewed by the principal investigator and the biostatistician prior to publication to avoid violation of patients’ rights.

## Ethics statement

The study will be performed in accordance with the Declaration of Helsinki and will comply with the International Conference on Harmonization and Good Clinical Practice. The CC-3 study was approved by the Ethics Committee of the Medical Faculty of the Heinrich Heine University Düsseldorf and the Paul-Ehrlich-Institut, Germany (P00702).
